| Criteria for evaluation:  Safety: Safety will be assessed by the Clavien-Dindo classification and reporting of Adverse Events.  The maximum tolerated dose of 5-FU will be determined by giving the first 15-30 patients escalating doses of 5-FU. The morbidity of each dose level of 5-FU 24-hour EPIC will be evaluated by the Data Monitoring Committee 30 days post-treatment. A dose level with ≤1/3 or ≤2/6 with 3b-4 Clavien-Dindo morbidity may proceed to the next dose level. Following the dose titration study, all patients will receive the maximum dose of 5-FU. An interim safety evaluation will be performed after the first 140 patients have been randomized and treated with HIPEC or HIPEC in combination with EPIC. The Clavien-Dindo grade 3-5 morbidity is expected to be approximately 0.35 (35%). If the experimental arm’s 95% CI falls within 0.4 or below, the study will be allowed to continue.  Efficacy: Recurrence free survival (RFS) is determined at 12-months post treatment through the HIPEC registry. Postoperative complications rates with-in 30 days, 5-year overall survival and RFS are further determined through the HIPEC registry and quality of life is assessed by questionnaires through the QoL registry. | | |
| **Dosage of Investigational Products:**  The maximum tolerated dose (MTD) of 5-FU will be determined by giving the first 15-30 patients escalating doses of 5-FU. The morbidity of each dose level of 5-FU 24-hour EPIC will be evaluated by the Data Monitoring Committee within 30 days post-treatment. A dose level with ≤1 of 3 patients or ≤2of 6 patients (extended group size) with 3b-5 morbidity may proceed to the next dose level. If the frequency of 3b-5 morbidity is higher, MTD has been passed and the dose of 5-FU in the efficacy study will be the next lower dose level. If MTD is not reached the highest dose level of 5-FU (850 mg/m^2^) will be used. | | |
| Statistical methods:  Recurrence free and overall survival of the two arms will be compared using the parameters: treatment arm, age, PCI, CC score, use of systemic perioperative chemotherapy (neoadjuvant and/or adjuvant), concomitant liver metastases resection, colon or rectal primary tumor, and lymph-node metastasized primary tumor.  QoL will be analyzed by comparing the answers to questions 29 and 30 in QLQ-C30 by Mann-Whitney U test and Freidman’s repeated measures ANOVA test. Specifically, differences between the sexes will be investigated.  Statistical significance will be set at p=0.05. | | |

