#### Health-related quality-of-life assessment

EORTC QLQ-C30 and CR29 and STO22 forms will be used to evaluate quality-of-life [10]. These forms will be sent out at baseline, 3, 12, and 36 months. The primary outcome is the comparison of questions 29 and 30 from the QLQ-C30 at 12 months rated 1-7, where 1 is very poor and 7 is excellent.

QLQ-C30 questions for QoL assessment:

29. How would you rate your overall health during the past week?

30. How would you rate your overall quality of life during the past week?

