##### Secondary outcome analyses of overall survival and QoL:

- Overall survival up to 5 years will be compared with Kaplan-Meier and log-rank test as well as multivariable Cox regression using the following same variables as RFS: Treatment arm, age, PCI, use of systemic perioperative chemotherapy (neoadjuvant and/or adjuvant), liver metastases resection, colon or rectal primary, and lymph-node metastasized primary tumor.
- Quality of life between the two arms will be compared. The primary outcome is the comparison of questions 29 and 30 from the QLQ-C30 at 12 months and 36 months. The primary statistic will be a Mann-Whitney U test of difference for both question 29 and 30 between the arms. The secondary statistic will be a comparison of mean differences for question 29 and 30 between baseline and 12-months using a Freidman’s repeated measures ANOVA test. Specifically, differences between the sexes will be investigated.
- Three specific subgroup multivariable analyses using RFS as endpoint will be performed using the same variables as above for correction: (1) PCI score – the score will be grouped 1-10, 11+, (2) Signet cell cancer, (3) previously given oxaliplatin-based therapy, (4) +/- livermetastases.
- Further exploratory and post hoc analysis of subgroups will be performed: multivariable analysis for overall survival and forest plots.

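### The secondary quality-of-life statistic, a Friedman test of baseline against 12 months, has no treatment-arm term and so cannot serve the stated between-arm aim (minor)

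*Protocol*

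**What the plan says.** The QoL item in section 13.2.1 (secondary outcome analyses of overall survival and QoL) opens with a between-arm aim: "Quality of life between the two arms will be compared". It then names two statistics.

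- Primary: "The primary statistic will be a Mann-Whitney U test of difference for both question 29 and 30 between the arms".
- Secondary: "The secondary statistic will be a comparison of mean differences for question 29 and 30 between baseline and 12-months using a" test that the sentence names at its end, "using a Freidman’s repeated measures ANOVA test". The spelling is taken to mean Friedman's test.

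The sentence on the secondary statistic mentions two time points. It mentions no arm, no arm-by-time term and no comparison of change between arms. The synopsis (statistical methods) lists the same pair of tests, "by Mann-Whitney U test and Freidman’s repeated measures ANOVA test", and adds no arm term either.

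Section 11.1.1 describes the response scale: "at 12 months rated 1-7, where 1 is very poor and 7 is excellent". Questionnaires are collected at baseline and at 3, 12 and 36 months (sections 8.3 and 11.1.1). QoL is a secondary objective and endpoint (sections 6.2 and 7.2).

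**The concern.** A test placed under a between-arm aim should contain the arm. Friedman's test ranks the repeated scores of each patient and asks whether the ranks differ between occasions. It can say that scores moved between baseline and 12 months. It cannot say that they moved differently under intensified treatment than under standard treatment. The sentence also speaks of mean differences, which a rank test does not estimate.

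Section 16.2 uses QoL to follow how patients experience the balance of side effects and benefit in an intensified regimen. Of the two QoL statistics, this is the only one that uses the baseline score. If its result were taken as the arm comparison announced at the start of the item, a time trend common to both arms could pass for a treatment effect, or a real difference between arms could go unseen.

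**Working it through.** The protocol gives no QoL effect size, SD or power, so there is no QoL figure to reproduce. The check has two parts: the algebra of the test, which needs no assumption about effect size, and a simulation to show scale.

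**1. What the test reduces to.** Let n+ patients score higher at 12 months than at baseline, n− score lower, and n0 stay the same, with n = n+ + n− + n0 and k = 2 occasions.

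- Within-patient ranks are (1, 2) for a rise, (2, 1) for a fall and (1.5, 1.5) for a tie.
- The rank sum at 12 months departs from its expectation 1.5n by (n+ − n−)/2; at baseline the departure is the negative of this. The sum of squares is (n+ − n−)²/2.
- The tie-corrected denominator is the sum of squared ranks minus nk(k+1)²/4, that is 5(n+ + n−) + 4.5·n0 − 4.5n = 0.5(n+ + n−).
- The statistic is (k − 1) × [(n+ − n−)²/2] / [0.5(n+ + n−)] = **(n+ − n−)²/(n+ + n−)** on 1 degree of freedom.

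This is the sign test on change. A numerical check on 100 random pairs of 1–7 scores gave p = 0.8312 from the full Friedman formula and from the short form. Arm appears nowhere.

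**2. What that means for two arms pooled.**

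- Both arms have a rises and b falls, so there is no difference between arms. The statistic is (2a − 2b)²/(2a + 2b) = 2(a − b)²/(a + b), which grows as a and b move apart.
- One arm has a rises and b falls, and the other has b rises and a falls. Then n+ = n− = a + b and the statistic is 0, however far apart the arms are.

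**3. Scale, by simulation.** From section 13.3: 163 randomised or 148 evaluable per arm (numbers set for recurrence-free survival, not QoL). From section 13.4: a 5% level, taken as two-sided. From section 11.1.1: the 1–7 scale. Assumed, not in the protocol: baseline mean 5, SD 1.3, within-patient correlation 0.5, the shifts shown, and 110 per arm as a smaller case. There were 4,000 trials per row.

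Pooled Friedman test, % of trials with p < 0.05:

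| Change in arm A / arm B | 163 per arm | 148 per arm | 110 per arm |
|---|---|---|---|
| 0 / 0 | 5.2 | 5.1 | 5.6 |
| −0.25 / −0.25 | 84.2 | 81.2 | 68.1 |
| −0.5 / −0.5 | about 100 | about 100 | 99.8 |
| +0.5 / +0.5 | about 100 | about 100 | 99.8 |
| −0.4 / +0.4 | 3.9 | 4.5 | 4.6 |

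A second run (2,000 trials, 120 per arm, correlation about 0.5) gave 88.8% when both arms fell by 0.3 and 3.9% with changes of +0.3 and −0.3. It is used only as support, because its assumed mean and SD are not stated.

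**4. Running it in each arm separately.** With the same 0.25-point fall in both arms, exactly one of the two arms was significant in 50.4% of trials at 163 per arm (50.1% at 148, 48.0% at 110). Setting one p-value against the other is therefore not a valid comparison of arms either.

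**5. A statistic that contains arm.** A Mann-Whitney test of the 12-month minus baseline change between arms rejected in 4.5 to 5.1% of trials at 163 per arm when both arms changed equally (4.3 to 5.6% over all three sizes). With changes of −0.4 and +0.4 it rejected in 99.8% at 163 per arm and 98.5% at 110.

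**The case against.** The strongest reply is that the arms are compared, and validly, by the primary statistic. That stands. Randomisation makes the unadjusted Mann-Whitney test valid. In the 120-per-arm run, applied at 12 months, it rejected in 5.3% of trials with no arm difference and in 93% with changes of +0.3 and −0.3. A reader might infer that the whole QoL analysis fails to compare the arms; the protocol does not support that. Nor is it an error that this test leaves out baseline. That costs precision and causes no bias.

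A reader might also infer that the trial will report time trends as treatment effects. The protocol does not say so. Read as a description of change over time, the Friedman test is valid; it simply does not serve the aim under which it stands. The rule in section 13.2.1 that any significant analysis supports a conclusion comes before the QoL item and concerns locoregional effect, so it does not reach QoL.

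The words ANOVA and mean differences might suggest that a repeated-measures ANOVA with arm as a factor was intended. The text names Friedman's test in both places and no arm factor in either, so that intention would have to be written down.

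The heading of the main efficacy analysis refers to an updated plan in an appendix that is not at hand, and that appendix may have changed this item. In the text at hand, however, the recurrence-free survival items are struck through and the QoL item is not, and the synopsis still lists the test.

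Finally, the percentages depend on assumed inputs, and exactly opposite changes are the extreme case of cancellation. Both points are fair; the absence of arm from the statistic depends on neither.

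**Conclusion.** The point holds in a limited form. The secondary QoL statistic is the wrong kind of test for the between-arm aim: it has no arm term, it is a sign test of change over time, and it does not compare mean differences. This follows from the form of the test alone.

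The size is illustrative. With an equal fall of 0.25 to 0.3 points in both arms, rejection was about 84% (163 per arm) to 89% (120 per arm), and 68% at 110 per arm. With equal and opposite changes it was about 4%. Misleading conclusions would follow only if scores shift over time and the result is read as a treatment comparison.

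Severity is minor. The primary QoL test is sound, and the defect touches neither the primary endpoint nor the sample size. The conclusion assumes that the unseen appendix leaves the QoL item unchanged.

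**What to change.** In section 13.2.1 and the synopsis, replace the Friedman test with a between-arm comparison that uses baseline. Examples are ANCOVA or a proportional-odds model of the 12-month score on arm and baseline score, for each of questions 29 and 30. Comparing the 12-month minus baseline change between arms would also suffice.

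Of these, adjusting for baseline is the more precise. With equal SDs at both times and an assumed correlation of 0.5, the variance relative to a 12-month-only comparison is 1 − 0.5² = 0.75 for ANCOVA and 2 × (1 − 0.5) = 1.00 for change scores.

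The primary Mann-Whitney test can stay. If a Friedman or sign test is kept, label it a description of change over time and not a treatment comparison. If the appendix already makes this change, bring section 13.2.1 and the synopsis into line with it.

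The cost is wording only, since baseline and 12-month questionnaires are already collected.

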## Determination of sample size

Dose titration study

15-30 patients depending on how many dose levels require 6 patients.

Interim trial safety evaluation

140 patients (70 in each arm) which is close to 50% of the sample size for an extended safety analysis. See 13.2.1.2.

Efficacy study

Using an alpha of 5% and beta of 80% and a 12-month recurrence free survival benefit from 50% till 66% from a recent retrospective study comparing Ox HIPEC vs Oxiri HIPEC for colorectal cancer (figure 1, [6]), 148 patients is needed in each arm. With 10% loss to follow up or violation rate, 163 patients in each arm will be needed. In total, 326 patients are to be included in the colorectal cancer group which will define the sample size.

In total, approximately 341-356 patients will be recruited for the phase I/III trial which will be included from 4 centers with the following estimations:

Uppsala – 114-118 patients

Stockholm – 114-118 patients

Malmö – 57-59 patients

Göteborg – 57-59 patients

Aarhus – patient count pending

Oslo – patient count pending

The CRS and HIPEC operation rate in Sweden is approximately 180 patients/year. Two-thirds are diagnosed with colorectal cancer leaving 120 potential candidates to be included in the study. If we manage a 90% inclusion rate, the dose titration part of the trial will take 6 months followed by another 4.5 years to study efficacy (see 20.5 for further details). The trial program will take approximately 5 years to complete.

##

## Statistical significance

The statistical significance level will be set at *p*=0.05.

## Criteria for the termination of the trial

If no numerically and clinically relevant differences are found in either RFS, overall survival, peritoneal RFS, or pattern of recurrence at 12 months or during the whole study follow-up, then the study can be deemed futile and may be closed prematurely at the time of the interim analysis.

## Missing data management

If missing data is identified during study data acquisition, then it may be pertinent to consult hospital charting to rectify missing data. However, if the data is not available and cannot be acquired, then a multiple imputation analysis may be performed.

## Intention-to-treat analysis

The trial will be intention-to-treat. Thus, all patients being randomized are included in the trial. Since treatment is administered within hours of randomization, there will likely be no or minimal fallout of subjects between randomization and treatment administration.

# Direct access to source data/documents

The Investigators/institutions will permit study-related monitoring, audits, review and regulatory inspections, providing access to source data/hospital records. Sponsor verifies that each patient has consented in writing to direct access to the original source data/hospital records by the use of written patient information and signed Informed Consent, which also includes remote access via NPÖ (Nationella Patient Översikten).

During the monitoring, the data recorded in the HIPEC registry (and eCRF section) will be controlled for consistency with the source data/hospital records by the study monitor (source data verification). Any discrepancies of data will be documented and explained in the monitoring reports. The data that is to be monitored has been specified in the section 13.1 “Data Management”.

As the sponsor representative and coordinating investigator is the same person, access to source data is available also for the sponsor. All site investigators are required to register the data in the HIPEC registry as determined by this protocol. If problems with registering data occur, the study monitor may do a site visit in order to acquire the necessary data for completing the required analyses.

# Quality control and quality assurance

This trial program will employ a regional clinical trial unit (UCR - Uppsala Clinical Research Center) with many years of experience in running and setting up randomized clinical trials as well as registry-based randomized trials. Preliminarily, UCR will conduct the trial monitoring as well as support all necessary documentation and procedures needed to pass Swedish regulatory requirements.

## Source data

The following minimum amount of information should be recorded in the hospital records (the relevant hospital charting which includes this information is specified in the section 13.1):

- Clinical study number. (Preoperative visit)
- Subject identification. (Preoperative visit)
- Date when patient information was given and when signed Informed Consent was obtained. (Preoperative visit)
- Diagnosis. (Preoperative visit)
- Fulfillment of inclusion criteria. (Preoperative visit)
- Specification of visit dates, concomitant medication and any AEs. (Medication and blood chemistry results)
- Specification of study treatment and doses given. (Operating notes)
- Specification of the subject’s cessation in the study (e.g. withdrawal from follow-up).

Since the trial is registry based, the follow-up does not require separate eCRF evaluations. These evaluations can be automatically retrieved from the registry – both recurrence data, quality of life, and morbidity data.

## Monitoring

In accordance with the principles of Good Clinical Practice (GCP), monitoring of the study will be arranged by the Sponsor. During the study, the Monitor will have regular contacts with the study site(s), including visits to ensure that the study is conducted and documented properly in compliance with the protocol, GCP and applicable regulatory requirements. The HIPEC registry and quality-of-life registry will be monitored for consistency. The monitor work will be described in a monitoring plan.

The study sites may also be subject to quality assurance audit by the Sponsor as well as inspection by the MPA. The site Principal Investigator and other responsible personnel must be available during monitoring visits, audits and inspections and should devote sufficient time to these processes.

All study personnel should provide a curriculum vitae (CV) or equivalent documentation of suitability for their responsibilities in the study. All Investigators and other responsible personnel should be listed together with their function in the study on the signature and delegation list.

# ETHICS

## Ethical review authority

It is the responsibility of the Sponsor to obtain approval of the study protocol/protocol amendments, the patient information and the Informed Consent from the ERA before enrolment of any subject into the study.

## Ethical Conduct of the study

The study will be conducted in accordance with the protocol, applicable regulatory requirements, GCP and the ethical principles of the Declaration of Helsinki as adopted by the 18^th^ World Medical Assembly in Helsinki, Finland, in 1964 and subsequent versions (Appendix 21.5).

The main ethical considerations in this research project are related to the balance of procedural morbidity/mortality and efficacy/benefit. CRS and HIPEC treatment is a morbid procedure in itself, thus it is important to monitor that the morbidity does not lead to increased postoperative mortality. Furthermore, it is important that morbidity does not lead to increased long-term functional handicap. Most morbidity involved in this procedure is temporary. Out of 9 previous studies on EPIC, 3 studies indicated that there may be increased morbidity (but none for mortality) [7]. The other 6 studies showed no difference. The largest study [6] (group E is comparable to the intensified HIPEC arm in this protocol) shows no morbidity difference, no mortality difference, and no increased reoperation rate either. As such, it is not anticipated that this study will lead to a general increase in morbidity or mortality. However, this intensified HIPEC arm has not been followed up in a prospective systematic way. Neither has the maximum tolerated dose for a 24-hour 5-FU been determined. Therefore, this trial will begin as a phase I study that moves into a randomized open-label phase III study. During an interim analysis after half the patients in phase III part have been included, the morbidity results will be reviewed by the DMC before finishing the phase III step.

One specific morbidity that has been raised concerning intensified HIPEC treatment is neutropenia [11]. This is a specific morbidity that most likely will be increased with the intensified treatment. However, a recent study [8] investigating the specific effects of neutropenia showed that other serious side-effects were not increased nor mortality. Unexpectedly, neutropenia was a positive prognostic factor. Moreover, the effects of neutropenia are temporary and mitigated relatively easily with granulocyte-colony stimulating factor. Lastly, to monitor the patient’s perspective on the side-effect/benefit balance, a quality-of-life part of the trial will be included in order to follow-up health-related quality-of-life.

## Risk - benefits

As seen in the safety review from an earlier study [7] in Table 2, the morbidity of adding EPIC treatment to HIPEC is inconclusive. A few studies have shown increased morbidity while others have not. Due to the logistical problem of chemotherapy administration on the surgical wards and the possible morbidity increase, the EPIC treatment will be decreased from the standard 5 days to a one-time administration at the end of surgery. This will alleviate any potential increased risks with adding EPIC treatment to HIPEC.

**Table 4. Table 2 from Systematic Review [7]:**

Studies comparing HIPEC to the combination of HIPEC + EPIC (for 5 days) for lower gastrointestinal tumors with peritoneal metastasis following cytoreductive surgery.

| **Author, year, country** | **Origin** | **n** | **Treatment regimen** | **Grade 3 + morbidity** | **Survival analysis** |
| --- | --- | --- | --- | --- | --- |
| Glehen International | Colorectal | 271 112 | HIPEC HIPEC + EPIC | EPIC=more fistulasRR 1.7. p=0.032 | HIPEC + EPIC Better than HIPEC and EPIC alone but NS p=0.61 |
| Saxena Australia | Colorectal | 12 34 | HIPEC HIPEC + EPIC | 50% NS 30% | Not reported |
| Chua international | PMP | 1382 668 | HIPEC HIPEC + EPIC | No difference | HIPEC found to be an independent factor of better OS but not EPIC |
| Chua Australia | Colorectal Subgroup^a^ | 30 45 | HIPEC HIPEC + EPIC | 13% 16% | 19 months RFS. 19 months OS 33 months RFS. 38 months OS p=0.046. p=0.38 |
| Lam [12] Canada | Colorectal + High grade appendix | 37 56 | HIPEC HIPEC + EPIC | 19.6% p=0.01 43.2% | 6% 3Y RFS 46% 3Y OS. 21% 3Y RFS 50% 3Y OS. NS. NS |
| Sparks Australia | Appendix | 13 17 | HIPEC HIPEC + EPIC | Trend toward more complications with EPIC group NS | No difference |
| Tan Singapore | multiple | 69 42 | HIPEC HIPEC + EPIC | 25% p=0.048 58% | Not reported |
| Huang Australia | LAMN | 74 176 | HIPEC HIPEC + EPIC | 44.6% 48.3% | 64.5% 5Y OS. p=0.001 93.0% 5Y OS |
| Huang [13] Australia | PMCA | 118 67 | HIPEC + EPIC | 47.9% 53.7% | 30.5% 5Y OS. p=0.003 62.3% 5Y OS |

^a^Appendiceal neoplasms reported in later case control studies of the same unit.

HIPEC, Hyperthermic intraperitoneal chemotherapy; EPIC, Early postoperative intraperitoneal chemotherapy; NS, Non statistically significant; PMP, pseudomyxoma peritonii; OS Overall survival; RFS, Recurrence free survival; LAMN, Low-grade appendiceal mucinous neoplasm; PMCA, Peritoneal mucinous carcinomatosis of the Appendix.

An international collaboration on colorectal cancer with peritoneal metastases has demonstrated in manuscript format [6] that there is no increased morbidity connected with intensifying the HIPEC treatment both in terms of dual HIPEC drugs (oxaliplatin and irinotecan HIPEC) and in terms of adding EPIC (1-5 days of 5-FU) to the dual drug HIPEC treatment. Most importantly, there is no increased risk of mortality [6].

One morbidity that has been discussed separately is neutropenia. In a previous study conducted in France, the main increase in morbidity between oxaliplatin HIPEC and oxaliplatin/irinotecan HIPEC was neutropenia [11]. However, the risk of neutropenia was alleviated with G-CSF and it did not lead to increased mortality nor to an increase in other grade 3-4 adverse events. A new study has investigated the potential harm of postoperative neutropenia after HIPEC and not only did it not lead to increased other Clavien-Dindo grade 3-5 morbidity, but it was also a positive prognostic factor for treatment outcome [8].

As seen in Figure 1 in the beginning of the protocol, the survival benefit is significant between Single drug oxaliplatin HIPEC vs double drug HIPEC+EPIC. The estimated benefit gives a hazard ratio of 0.81, *p*=0.022.

The intensified arm (oxiri HIPEC + 5-FU EPIC) has been in use already within routine clinical practice primarily from one French institution that has treated 96 patients[6]. However, the use of single oxaliplatin HIPEC + 5 days of 5-FU EPIC has been in widespread use in many institutions, including Swedish clinics [5]. Our modified arm has only 1 day of EPIC instead of 5. Thus, the expected morbidity should be even less, and it is the view of the Study Committee that the potential benefits in a significant way outweigh the potential increased risk. However, in order to verify this systematically, the trial will have a two-step design – first a phase I dose-titration study to find the best 24-hr EPIC dosage of 5-FU; thereafter, follows a phase III open-label randomized trial.

An assessment of conducting this trial during the COVID-19 outbreak has been performed. All patients included in this trial will already be going for surgery and will receive a HIPEC treatment regardless of the current outbreak. This treatment is considered imperative. The only identifiable difference to date is the postoperative neutropenia which separates the experimental arm from the standard arm. However, due to the extensive surgery, all patients will be continuously monitored in-hospital until the postoperative neutropenic period is over. The anticipated start date for this trial will be after all hospital personnel in Sweden have received COVID-19 vaccinations. The risk/benefit ratio is therefore found to be in favor of trial continuation. One adjustment has been made per suggestion from the “GUIDANCE ON THE MANAGEMENT OF CLINICAL TRIALS DURING THE COVID-19 (CORONAVIRUS) PANDEMIC”. In order to decrease the need for travel, the 90-day follow-up may be performed via telephone or videocall unless there is an adverse event needing physical examination.

